**Figure 1 figure1:**
[figure not shown]
Screenshot of the eight “decks” of virtual cards in the “What Do You Know?” psychoeducation activity. Clinicians and families select the most pertinent decks for each child. The cards within each deck are customizable by the clinician to enhance relevance to each family’s needs.

**Figure 2 figure2:**
[figure not shown]
An example card from the Domestic Violence deck. Users can swipe left or right through the deck to view additional cards. A scoreboard is presented at the bottom to increase engagement.

**Figure 3 figure3:**
[figure not shown]
A Provider tab is located at the top of the screen and contains specific notes for each card. These notes may be used as discussion points during session.

**Figure 4 figure4:**
[figure not shown]
At the end of each activity, progress is tracked graphically via color-coding (ie, green=complete). On this page, module-specific homework assignments may be assigned. The Menu button at the top of each screen allows users to access the Home screen or end a session and assign homework.

**Figure 5 figure5:**
[figure not shown]
One activity in the Affective Regulation module involves directing the child to list as many different feeling words in 90 seconds as he or she is able to. This activity uses a free-write function. The Provider tab at the bottom of the screen provides tips for clinicians on strategies for using this activity effectively in session.

**Figure 6 figure6:**
[figure not shown]
Another Affective Regulation activity is Feelings Charades. Users “spin” a virtual wheel by dragging down on the feeling words. They are then instructed to act out the feeling on which the wheel lands. A scoreboard is available to increase engagement with the activity.

**Figure 7 figure7:**
[figure not shown]
An activity in the Cognitive Coping module has children practice identifying and categorizing thoughts, feelings, and behaviors by dragging the words and phrases on the left of the screen (shown in gray) to the appropriate icon on the right of the screen. Feedback is provided in response to each user interaction.

### Phase III: Feasibility Trial

#### Approach

The goal of the ongoing feasibility trial is to examine the feasibility of implementing the TF-CBT e-workbook in community mental health service agencies, and to demonstrate the randomized controlled trial (RCT) methodology we propose to use in a future large-scale trial to test the effectiveness of the TF-CBT e-workbook in clinics across the state. Resources and data resulting from this project are designed to position us well for a large-scale RCT to examine the incremental benefit of e-workbooks to best-practice interventions compared to standard care without technology. The strengths and limitations associated with conducting a small-scale feasibility RCT versus an open trial were carefully considered. A major benefit of the latter approach included increased quantity of feasibility data related to the use of the e-workbook. On balance, this option was outweighed by the importance of demonstrating the feasibility of the full RCT methodology. This would allow us to identify and address barriers in recruitment, retention, fidelity assessment, and other procedures essential to successful conduct of a RCT. This approach is consistent with expert recommendations to pilot test the feasibility of methods to be used in large RCTs, use data yielded by such studies to “debug” the methodology, and assess optimal strategies to executing the RCT [44].

#### Design

The feasibility trial will involve 10 providers recruited from four participating community-based mental health and child welfare agencies where TF-CBT is delivered. Providers will have been fully trained in TF-CBT and carry active child trauma cases at the onset of the trial. Providers will be block randomized by site to either the e-workbook facilitated TF-CBT (n=5) or standard TF-CBT (TAU) (n=5) conditions. Each provider will treat at least two children for a total sample of 20 children. We will also pursue an exploratory aim regarding the feasibility of using the e-workbook across multiple treatment delivery settings by including a small subsample of mental health providers who are primarily based in school settings (at least two per study condition).

An independent, trained evaluator who is blind to the study condition will conduct baseline, mid-treatment, and post-treatment clinical assessments. Families will be reimbursed $30 for each administration of the assessment battery. All sessions will be audiorecorded and coded for fidelity and child engagement by independent coders.

Alternatives to this design decision were considered carefully. For example, the design could have included each provider treating one e-workbook case and one standard TF-CBT case, with randomized ordering of conditions by provider. An advantage of this approach is that provider factors are less likely to have strong impact on clinical outcomes in this small-scale trial. A weakness of the approach is that use of the e-workbook could affect performance on subsequent standard TF-CBT cases for providers assigned to deliver TF-CBT using the e-workbook first. Additionally, it was determined that if providers within an agency were assigned to different starting conditions, this could increase risk of contamination across conditions with standard TF-CBT providers hearing about, viewing, and potentially even using elements of the e-workbook with standard TF-CBT cases. Overall, it was concluded that block randomization by clinic to the two study conditions was a preferable design strategy.

#### Participants

##### Providers

A minimum of 10 providers who have been trained in TF-CBT and maintain active child trauma caseloads will be recruited from four participating clinics in the Charleston tri-county area. The clinics include both outpatient mental health clinics and child advocacy centers. We will make every effort to recruit a racially/ethnically diverse sample of providers to allow integration of feedback from providers with diverse backgrounds. We will also attempt to recruit a balanced sample with respect to sex and gender. Inclusion criteria for providers will be as follows. Providers will be full- or part-time employees of the participating clinic and had to have obtained at least a Master’s degree in social work, counseling, clinical psychology, or a related field. Each provider will provide treatment to at least two study cases during the feasibility trial. Providers will be encouraged to enroll up to 5 children to increase the likelihood that at least 2 cases will be completed per provider during the trial.

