^a^Many items in the *recommendations* column already have been addressed by the development team. Recommendations made by several providers, such as the ability for providers to organize decks and create new cards in the “*What Do You Know?”* game and the recommendation to add decks addressing Internet safety and cyberbullying, were addressed by the developers in the revised e-workbook prior to the feasibility trial. Other recommendations were only voiced by one or two participants, and were considered on a case-by-case basis. Some observations made by providers related to child age; however, these observations often contradicted the perceptions of children. For example, some providers felt that two or three of the chapters were best for children under 12 years of age; but in each of these cases older adolescents (aged 13-16 years) responded very favorably to the chapters. We have informed providers of this feedback from adolescents and have asked providers to be open-minded in the context of the feasibility trial about the value of each resource on the basis of age.

**Table 3 table3:** Summary of qualitative feedback from children (n=24) during alpha testing.

e-workbook component (activity)	Positive feedback (children)	Recommendations^a^ and observations (children)
Psychoeducation (What Do You Know? card game)	Using technology would help kids be more comfortable	Audio narration that reads card to you
	Most youths said that they would like the iPad-based version over the real cards	Too much white background—include more colors and enhance flexibility
		Add more colors or brighter colors
		Have themes or animation that relates to the question OR that the kid can choose to “make it their own”
Psychoeducation (You Are Not Alone activity)	N/A—Children were not asked about this activity	
Psychoeducation (Your Body activity)	N/A—Children were not asked about this activity	
Relaxation (breathing/PMR Coaching activity)	Activity makes sense	Balloon is fine, maybe integrate other graphics, like lungs, or a kid breathing in and out
	Would be helpful to learn to calm down	Change white screens to something else—have options for different background colors (preferred neon)
	App version is very straightforward	Make activity available to kids/teens at home
	Like that they can practice many times	Drawn images of children should look more like a real person
	Appropriate for full age range of youth	Have a total body video
		Have buttons in order of muscle groups

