##### Patients

A minimum of 20 children aged 5-15 years and their caregivers will be recruited into the feasibility trial. These children will be recruited from participating clinics in the local area. We will make every effort to recruit a racially/ethnically diverse sample of youth (eg, >25% African American) to ensure integration of feedback from patients with diverse backgrounds. Inclusion criteria will be as follows. Participating children will be aged 5-15 years, have experienced at least one potentially traumatic event (eg, sexual assault, physical assault, witnessed violence, disaster, serious accident), and have at least one symptom on each PTSD symptom cluster (re-experiencing, avoidance, hyperarousal) based on a diagnostic interview. Cases will be excluded when the child or caregiver exhibits psychotic symptoms (eg, active hallucinations, delusions, impaired thought processes); significant cognitive disability, developmental delays, or pervasive developmental disorder; or active suicidal or homicidal ideations. Children also will be excluded when there is no consistent caregiver available to participate (eg, short-term foster care placement, restrictions by child protective services). These criteria are consistent with those used in prior TF-CBT clinical trials.

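### Randomised providers, who by strong implication know their condition, enrol their own cases, so child case mix is not protected by randomisation and the recruitment measure cannot reveal selective offering

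*Protocol article*

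**What the plan says.** All places are in the protocol article, Phase III.

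- **Unit randomised (Design).** "Providers will be block randomized by site to either the e-workbook facilitated TF-CBT (n=5) or standard TF-CBT (TAU) (n=5) conditions". The same section later says that "block randomization by clinic to the two study conditions was a preferable design strategy". Children are not randomised under either wording.
- **Who enrols, and how many (Design; Providers).** "Each provider will treat at least two children for a total sample of 20 children", and "Providers will be encouraged to enroll up to 5 children to increase the likelihood that at least 2 cases will be completed per provider".
- **Where the children come from (Design; Patients).** "Providers will have been fully trained in TF-CBT and carry active child trauma cases at the onset of the trial". The Patients section adds, in the passive, "These children will be recruited from participating clinics in the local area".
- **Safeguards (Design; Patients; Assessment).** Eligibility rests on fixed criteria, with the symptom requirement set by diagnostic interview. "An independent, trained evaluator who is blind to the study condition will conduct baseline, mid-treatment, and post-treatment clinical assessments". The Assessment section places baseline at the screening interview.
- **Recruitment measure (Data Analysis Plan).** Among the patient-level variables, the plan lists recruitment as a percentage of eligible patients. The definition that follows divides those who agree by those solicited.
- **Purpose (Purpose and Aims; Approach).** Aim 3 compares standard with iPad-facilitated treatment. The trial is also meant to demonstrate the method for a later large RCT, with recruitment among the procedures to be tested.

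**The concern.** Randomising providers balances, in expectation, what providers bring: skill, experience, style. It balances the children only if the route by which a child enters the study does not depend on the provider's condition. Here the enroller is the randomised person and delivers the condition, so cannot be blind to it. This is the usual recruitment problem of cluster-type designs.

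The article itself gives a plausible route. The footnote to Table 2 reports that "some providers felt that two or three of the chapters were best for children under 12 years of age", while eligibility in Phase III runs from 5 to 15 years. If such views influence which children are offered the study in the e-workbook arm only, the arms will differ in age. Attendance, attrition, engagement and fidelity can all depend on which child is treated, so a difference between arms, or none, could partly reflect case mix.

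The Design section weighs provider effects, carry-over and contamination, but not selective enrolment. A trial run to find weaknesses in the RCT method should be able to see this one.

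**Working it through.** **1. The plan's own figure.** (5 + 5) providers × 2 children = 20, which reproduces the stated sample.

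**2. What is left to enrolment.** With 2 to 5 children per provider, an arm of five providers holds 5 × 2 = 10 to 5 × 5 = 25 children, and the trial 20 to 50. Within that range, the numbers depend on how many cases each provider brings in.

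**3. Order of events.** The article does not say outright that allocation precedes enrolment. Two statements point that way.
- The evaluator is described as blind to condition at baseline, which is the screening interview. That means little unless the condition is already set.
- A provider keeps one condition while bringing in between two and five children. Unless all are enrolled before allocation, which the article does not describe, the later ones enter with the condition known.

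**4. Reach of the safeguards.**

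| Safeguard | Controls | Does not control |
|---|---|---|
| Fixed criteria, diagnostic interview | Who qualifies | Which qualifying child is offered the study |
| Blinded evaluator, including at baseline | How outcomes are measured | Who reaches the evaluator |
| Randomisation of providers | Provider characteristics, in expectation | Child case mix |

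**5. The recruitment measure.** For one provider or arm, let E be eligible cases, S those solicited and A those who agree. The announced quantity is A/E and the defined one is A/S. They are linked by A/E = (A/S) × (S/E). Selective offering acts through S/E, and through which children make up S. Neither enters A/S, so two arms could show the same A/S while offering the study to quite different parts of their caseloads.

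**6. Could a baseline comparison settle it?** Use the normal approximation, power = Φ(d√(n/2) − 1.96), two-sided 5%, with n children per arm and d the baseline difference in SD. The values of d are assumptions chosen to show a range; the document gives none.

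| d (assumed) | 10 v 10 | 25 v 25 |
|---|---|---|
| 0.3 | 10% | 18% |
| 0.5 | 20% | 42% |
| 0.8 | 43% | 81% |

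For example, d = 0.5 and n = 10 gives Φ(1.118 − 1.96) = Φ(−0.842) = 20%. Dividing n by the design effect 1 + (m − 1) × ICC, with assumed ICC of 0.05 to 0.20, takes the d = 0.5 row to 17–19% (m = 2) and 26–37% (m = 5). At the planned size, finding no baseline difference says little about whether selection occurred.

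**The case against.** The strongest reply is that this is a condensed article. A consecutive-case rule and consent procedures may stand in the full protocol, and their absence here is not itself a fault. The article does not say that providers choose which children to approach. The Patients section is passive on recruitment, and the Data Analysis Plan mentions contact between study staff and clinic staff about recruitment, so study staff have some role. The analysis only describes feasibility variables, and the Discussion defers efficacy to a later powered study.

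Much of this stands and limits the point. What remains rests on what is written: randomised providers are named as enrollers, and recruitment is defined on those solicited. If the full protocol fixes how cases are offered, the first part is answered. The mismatch between the announced and the defined recruitment measure is not.

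A reader might also infer more than the article supports:

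- *That the whole comparison is unprotected by randomisation.* Provider characteristics, which bear directly on fidelity, are randomised. Only child case mix is exposed.
- *That the bias can be sized.* Picking the best two of five would shift a mean by 0.83 SD with perfect judgement, or 0.25 to 0.50 SD at assumed correlations of 0.3 to 0.6. But five is an enrolment ceiling meant to offset dropout, not a pool from which two are picked. A provider who enrols all five has not chosen two of them. The correlations, and selection in one arm only, are also assumed.
- *That the target of two completed cases biases the arms.* It applies equally to both. It may favour families likely to stay, but that does not by itself separate the conditions.
- *That providers are known to select by age.* The remarks came from some Phase II providers about individual chapters. The article does not say that they take part in Phase III, and reports that providers were asked to keep an open mind.

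**Conclusion.** The point holds as a correctable design weakness. Child case mix is open to selection after allocation, the stated safeguards do not close that route, and the recruitment measure as defined cannot show whether it was used. It rests on one inference, that providers know their condition when they enrol. The text strongly implies this without stating it. It holds whether allocation is of providers within sites or of clinics, though those two wordings should be reconciled.

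No bias in SD units follows from the document, and none is claimed. Because the analysis is descriptive, no efficacy conclusion is at risk in this trial. The harm is to the by-arm reading of attrition, attendance, engagement and fidelity, and to the design's value as a template for the large RCT. The power figures above support only the statement that similar baselines would not rule selection out.

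**What to change.** **Providers section.** Require each provider, after allocation, to offer the study to consecutive eligible cases. Complete consent and the already planned blinded baseline before the family is told the condition.

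**Data Analysis Plan.** Keep a log for each provider of eligible cases not offered the study, with age and reason. Report recruitment by arm with all eligible cases as the denominator, so that the measure matches its description; the agreement rate among those solicited can stay as a second figure. Describe baseline age and PTSD score by arm, and state that the absence of a difference is not evidence that no selection took place.

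**Cost.** Providers lose some discretion, enrolment may be slightly slower, and there is a small logging burden. The blinded evaluator is already planned and the sample of 20 does not change. The log would also supply recruitment data of the kind this feasibility trial is run to collect.

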##### Patients

A minimum of 20 children aged 5-15 years and their caregivers will be recruited into the feasibility trial. These children will be recruited from participating clinics in the local area. We will make every effort to recruit a racially/ethnically diverse sample of youth (eg, >25% African American) to ensure integration of feedback from patients with diverse backgrounds. Inclusion criteria will be as follows. Participating children will be aged 5-15 years, have experienced at least one potentially traumatic event (eg, sexual assault, physical assault, witnessed violence, disaster, serious accident), and have at least one symptom on each PTSD symptom cluster (re-experiencing, avoidance, hyperarousal) based on a diagnostic interview. Cases will be excluded when the child or caregiver exhibits psychotic symptoms (eg, active hallucinations, delusions, impaired thought processes); significant cognitive disability, developmental delays, or pervasive developmental disorder; or active suicidal or homicidal ideations. Children also will be excluded when there is no consistent caregiver available to participate (eg, short-term foster care placement, restrictions by child protective services). These criteria are consistent with those used in prior TF-CBT clinical trials.

#### Assessment

A trained evaluator both blinded to treatment condition and fully trained in the administration of all measures will administer the assessment battery. All measures are well-validated and widely used instruments in the mental health field and in the treatment outcome research. Assessment will occur on three occasions: at baseline (ie, during the screening interview), at mid-treatment (ie, after the sixth treatment session, approximately two months post-baseline), and at post-treatment (ie, after the twelfth treatment session, approximately four months post-baseline). Treatment fidelity and child engagement will be measured via observational coding of audiotapes.

#### Treatment Fidelity

Fidelity to the TF-CBT and e-workbook-facilitated TF-CBT protocols will be measured via coding of audiotaped treatment sessions by independent, trained raters. Treatment sessions will be audiotaped for both study conditions (n=20 x ~10 sessions average=~200 audiotapes). Ratings will be completed using a behaviorally specific coding system of TF-CBT provider behavior that was modified for the current study to ensure relevance to the e-workbook condition [45]. The coding system will be used to calculate providers' fidelity to each TF-CBT component. An additional eight items focus on general therapy skills, not specific to TF-CBT, including establishing an agenda, providing a treatment rationale, and assigning homework. Additional items were created to identify use of the e-workbook activities to differentiate the two study conditions. Two independent raters will listen to audiorecorded treatment session tapes and complete the modified fidelity measure to code the use and extensiveness of specific treatment techniques depicted on the recordings. Raters will be trained in the coding system and meet biweekly throughout the remainder of the feasibility trial to ensure maintenance of acceptable levels of accuracy and interrater reliability. Discrepant ratings will be reviewed until consensus is achieved. If the two raters cannot reach consensus, the PI and Co-Is will make final decisions.

#### Child Engagement

Child engagement will be measured via coding of audiotaped sessions by independent, trained raters. The Child Involvement Ratings Scale (CIRS) [46-47], a 6-item scale that measures child engagement for each session, will be used for this purpose. Four “positive” involvement items and two “negative” involvement items are rated for each session on a 6-point scale (ie, “not at all” to “a great deal present”). The positive-involvement items emphasize the extent to which children initiate discussions, demonstrate enthusiasm, self-disclose, and demonstrate understanding. Negative-involvement items address withdrawal or avoidance in treatment. Coders will provide ratings based on two 10-min segments of session audiotapes (ie, beginning at min 10 and min 40). Child engagement ratings on the CIRS have been associated with clinical outcomes [47] and provider flexibility in delivery of EBTs [48]. Excellent internal consistency and strong interrater reliability have been reported for this measure [47-48].

